### Data analysis

In assessing primary outcomes (STI, HIV, and HCV incidence, unprotected sexual acts and unsafe injection acts), our over-arching modeling approach estimates intervention differences (HIVRR alone versus HIVRR+MF) longitudinally using a generalized estimating equations (GEE) approach, a flexible extension of conventional regression models, to account for repeated measures and clustering imposed by randomizing individuals in groups of six to eight women per cohort. STIs will be summarized as both a count (number of positive test results for any of the five STIs of interest (syphilis, gonorrhea, chlamydia, trichomoniasis, mycoplasma)) over the entire follow-up period, as well as a binary indicator of a positive test for any STI of interest at each follow-up time. The primary analysis will be a logistic GEE (e.g., presence/absence of an incident STI post randomization), accounting for clustering imposed by the study design in having women receiving their randomized intervention in cohorts of six to eight women each. Additionally, secondary analyses will consider intervention effects on HIV and HCV incidence as operationalized by binary indicators of testing positive for either, respectively, over the entire follow-up. We will employ logistic (binary outcomes) and Poisson (count outcomes) GEE models to estimate intervention effects as appropriate. We will implement an intent-to-treat approach for all analyses. Model estimates will be presented as estimates of incidence risk ratios or odds ratios, as appropriate, and corresponding 95% confidence intervals (CIs) and *p* values will be calculated for inference. Additionally, a logistic GEE modeling approach will be implemented for dichotomous outcomes (e.g., GEE with specified logit link) when evaluating the following outcomes: (1) self-reported unprotected vaginal and anal sexual acts with both regular and paying partners and (2) self-reported unsafe injection acts. Again, we will be interested in estimate rate ratios or odds ratios comparing HIVRR+MF to HIVRR alone. A Poisson GEE modeling strategy (e.g., GEE with specified log link) will be implemented to evaluate remaining secondary outcomes (1) self-reported number of unprotected vaginal and anal sexual acts with both regular and paying partners and (2) self-reported number of unsafe injection acts. To evaluate the secondary aims of the study related to potential moderating effects, we will expand these models to include “moderator X intervention” interaction terms along with the corresponding main effects and will assess examine the significance of each moderator on intervention effects through these interaction terms.

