#### Power and sample size

Power and sample size considerations for this proposal prioritized sufficiently powering the study to detect intervention effects on incidence for the following biological outcomes: STIs (syphilis, gonorrhea, trichomoniasis, chlamydia, and mycoplasma), HIV and hepatitis C virus (HCV). Using baseline prevalence estimates from our prior work in similar populations (e.g., 10%, 28%, and 75%, for STIs, HIV, and HCV, respectively) [29], we conservatively focused on the least prevalent of the three biological outcomes of interest, STIs. We noted that if we were sufficiently powered to estimate intervention efficacy for the least prevalent outcomes, we would also be sufficiently powered to detect intervention effects for the others. Using these prevalence estimates, we determined a range of plausible incidences based on our experience in similar settings. We first calculated crude (unadjusted for clustering by cohort) using a conventional approach to detect differences in a binary outcome (e.g., incidence) in two groups assuming an *α*-level of 0.05 for a two-sided hypothesis test of an overall intervention effect. Crude sample size estimates were then inflated by the “variance inflation factor” as described in Donner and Klar [30], to account for the likely correlation of outcomes induced by the study’s cluster randomized design. Finally, we adjusted 20% attrition over the 15-month follow-up. We considered scenarios of modest (intraclass clustering coefficient (ICC) equal to 0.005) and moderate (ICC = 0.01) clustering effects. In summary, we determined that randomizing 350 women in equal proportions to each intervention (175 to HIVRR and HIVRR+MF) would ensure that 80% power to detect true relative risks of 0.25 and ICC = 0.01. This attrition and clustering adjusted sample size corresponds to detecting STI incidence relative risks (RR) equal to 0.25 comparing women randomized to HIVRR+MF to HIVRR alone, where the assumed STI incidence over the study follow-up period is 0.043 and 0.144, respectively. In these calculations, the assumed incidence in HIVRR alone of 0.144 represents a decrease of approximately 40% from the estimated baseline prevalence of 28% from our prior work in this population [29]. Because the other biological outcomes of interest are more prevalent, we expect to have greater than 80% power to detect similar intervention effects.

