#### Cost-effectiveness analyses

Cost-effectiveness of the intervention will be analyzed based on STI infections and number of HIV and HCV cases averted over the 12-month period. We will compare cost-effectiveness of HIVRR+MF to HIVRR, using the cost of staff time, supplies, and overhead for the HIVRR and the MF interventions. We will calculate the incremental cost-effectiveness ratio between treatment *i* (HIVRR + MF) and *j* (HIVRR) in terms of outcome *k* by comparing extra cost with extra effectiveness in paired combinations: *ICERijk* = (*Ci* – *Cj*)/(*Eik* – *Ejk*) where *Ci* and *Cj* are the costs and *Eik* and *Ejk* are the effectiveness measures for treatments *i* and *j* measured along output *k*. This approach safeguards validity against any biased measurements of cost or effectiveness that are common to both *i* and *j* because they cancel out. Policymakers can easily and directly compare *ICERijk* to their existing costs and cost-effectiveness metrics to assess the added benefit of the microfinance intervention. We will also report total cost-effectiveness ratios for each intervention: *CERik* = *Ci/Eik*. To construct an effectiveness outcome of HIV, STIs, and HCV transmissions averted, we will use standard modeling procedures reported in HIV cost-effectiveness literature; i.e., a Bernoulli Process Model, the difference in risk-behavior frequencies times HIV transmission probabilities per act [31, 32]. One-way sensitivity analyses will use a range (e.g., 95% CIs) of HIV and HCV rates in the target population that may be compared to results to assess the robustness of estimates. Policymakers may compare the HIV, STIs, and HCV cost-effectiveness ratio to ratios for existing HIV interventions [31, 32] to ascertain the potential value of the microfinance intervention.

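### As written, the infections-averted formula applies an HIV per-act probability to STIs and HCV as well, so their cost-effectiveness ratios would be mis-scaled

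*Protocol article*

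**What the plan says.** All of the method stands in the protocol article under Cost-effectiveness analyses.

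- **Outcomes.** "Cost-effectiveness of the intervention will be analyzed based on STI infections and number of HIV and HCV cases averted over the 12-month period".
- **Ratio.** An incremental ratio (Ci − Cj)/(Eik − Ejk) is formed for each outcome k, where Eik and Ejk "are the effectiveness measures for treatments" i and j. A per-arm ratio Ci/Eik is also to be reported.
- **How the effectiveness measure is built.** "To construct an effectiveness outcome of HIV, STIs, and HCV transmissions averted", the article continues, "we will use standard modeling procedures reported in HIV cost-effectiveness literature; i.e., a Bernoulli Process Model", which it then describes as "the difference in risk-behavior frequencies times HIV transmission probabilities per act".
- **Sensitivity.** "One-way sensitivity analyses will use a range (e.g., 95% CIs) of HIV and HCV rates in the target population".

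Elsewhere, Data analysis makes STI the lead endpoint: "The primary analysis will be a logistic GEE (e.g., presence/absence of an incident STI post randomization". Table 1 and the Assessments section show that STI, HIV and HCV status is determined by laboratory assay at baseline, month 9 and month 15. Assessments also says that HCV was chosen as a marker of risk from drug use, whereas the five STIs serve as markers of sexual risk.

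**The concern.** One sentence promises an effectiveness outcome for three kinds of infection and then defines it with the per-act probability of one of them. Transmission per act differs by pathogen and by route, and the article itself assigns STIs to sexual risk and HCV to drug-related risk. Because the ratio is indexed by outcome k, each Eik needs its own input.

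At stake are the costs per STI and per HCV case averted, which the article offers to policymakers for comparison with other programmes. A modelled STI figure built on an HIV probability could also disagree with the STI difference that the same trial observes by assay and reports as its primary result.

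**Working it through.** **No cost-effectiveness figure to reproduce.** The article gives no per-act probability, act count, number averted or ratio, so the check is mainly on the text and the algebra.

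**1. What the formula does.** Let a_i and a_j be risk-act frequencies in the two arms and p_k the per-act probability for infection k. In product form the intended difference is |Eik − Ejk| = p_k × |a_i − a_j|. With the HIV probability in place of p_k it is

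p_HIV × |a_i − a_j| = (p_HIV/p_k) × intended difference.

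So the denominator is scaled by p_HIV/p_k, and the incremental ratio by p_k/p_HIV. If the same sexual acts are used for HIV and STIs, the formula as worded returns the same number averted for both.

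**2. Does it cancel?** The article says that measurement biases shared by both arms drop out of the ratio. That is true of an additive bias b: (E_i + b) − (E_j + b) = E_i − E_j. It is not true of a multiplier c: cE_i − cE_j = c(E_i − E_j). The multiplier also stays in Ci/Eik.

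**3. Would the sensitivity analysis show it?** It varies HIV and HCV rates in the population. No STI rate and no per-act probability is varied, so the STI ratio is untouched and the HCV ratio keeps the wrong multiplier.

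**4. Illustration of size.** Inputs from Power and sample size: STI incidence 0.144 (HIVRR) and 0.043 (HIVRR+MF), 175 women per arm. These incidences fit the stated total. The standard two-proportion formula at two-sided 0.05 and 80% power gives 130 per arm. Multiplying by 1 + (m − 1) × 0.01 and dividing by 0.8 gives 343, 345 and 350 women in total for cohorts of m = 6, 7 and 8. They imply 175 × (0.144 − 0.043) = 17.7 women with an STI averted.

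The per-act values below are **assumptions, not from the documents**. Solve 1 − (1 − p_STI)^n = incidence for n in each arm, then apply p_HIV to the same acts.

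Example at p_STI = 0.01:
- n = ln(0.856)/ln(0.99) = 15.5 and n = ln(0.957)/ln(0.99) = 4.4, a difference of about 11.1 acts.
- At p_HIV = 0.001: 175 × 11.1 × 0.001 = 1.9 averted instead of 17.7.
- Cost per STI averted is therefore 17.7/1.9, about 9 times too high.

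Factor on cost per STI averted (product form):

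| p_STI | p_HIV 0.0001 | 0.0005 | 0.001 | 0.005 |
|---|---|---|---|---|
| 0.005 | 45.4 | 9.1 | 4.5 | 0.9 |
| 0.01 | 91.0 | 18.2 | 9.1 | 1.8 |
| 0.05 | 464.5 | 92.9 | 46.4 | 9.3 |
| 0.1 | 954.1 | 190.8 | 95.4 | 19.1 |

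The factor is about 1 only where the two probabilities are equal. The direction follows from assuming p_HIV no larger than p_STI.

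**5. A second set of assumptions.** Choose 25 to 100 fewer acts freely, with p_HIV 0.0005 to 0.003. The formula gives 25 × 0.0005 = 0.0125 to 100 × 0.003 = 0.30 averted per woman, against 0.144 − 0.043 = 0.101. The cost would then run from about 8-fold too high (0.101/0.0125) to about 3-fold too low (0.30/0.101), a range that includes no error. Here the act differences are not tied to the incidences. The documents fix neither size nor direction.

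**The case against.** The strongest reply is that the clause is a loose one-line gloss on a method that the article names properly and supports with citations, and that a fuller protocol may hold infection-specific inputs. That may be so; the correction would then be one of wording. It does not clear the published sentence, which states a parameter rather than leaving one out. The section's opening sentence could also be read as using observed infections, but the sentence that constructs the outcome points to the model.

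Several stronger readings are tempting and are not supported:

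- **That the method is linear and not a Bernoulli process, and so could avert more than one infection per woman.** The article names a Bernoulli process model. For HIV-sized probabilities the product is also a fair approximation: for 100 versus 50 acts it overstates by about 1.04-fold at p = 0.0005 and 1.25-fold at p = 0.003. The dramatic figures (2.1-fold at 0.01, 35-fold at 0.05) need probabilities above that range. At 0.003, more than 333 fewer acts would be needed to exceed one infection.
- **That injection acts are left out for HCV.** The wording is risk behaviours in general, and the trial measures unsafe injection acts.
- **That women already infected are wrongly included.** The article is silent here, and its primary aim concerns new HIV and HCV cases. Its baseline prevalences ("75%, for STIs, HIV, and HCV, respectively", after 10% and 28%) do not settle it, since the same section later uses 28% as the reference for STI incidence.
- **That modelling from behaviour is illegitimate.** It is an accepted choice. The point for STIs is only that a direct measurement exists and should agree with the ratio.

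**Conclusion.** The point holds in a limited form. Applied as written, the rule uses an HIV per-act probability for STI and HCV transmissions averted. It would mis-scale the corresponding ratios by about p_k/p_HIV, and neither the differencing between arms nor the stated sensitivity analysis would reveal it.

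The factor of about 9, and the span from about 1 to about 950, rest wholly on assumed probabilities and should be quoted only as illustrations. A reader might infer that the trial's main STI result is compromised. It is not: cost-effectiveness is a secondary aim, and the logistic GEE on incident STI and the sample size do not use this formula. This is a desirable correction, not a threat to the trial's main conclusion.

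**What to change.** 1. **Cost per STI averted:** take the effect from the between-arm difference in laboratory-confirmed incident STIs, counted by the same rule as the primary endpoint, so that the ratio agrees with the primary result. State whether the unit is a woman with any STI or the number of positive results (both summaries are already planned). State also which window applies, since assays fall at months 9 and 15 while the cost-effectiveness section speaks of 12 months.
2. **Modelled HIV and HCV cases averted:** replace the HIV-only phrase with infection- and route-specific per-act probabilities, using injection acts for HCV, within the Bernoulli process model already named.
3. **Sensitivity analysis:** vary those per-act probabilities as well as the population rates.

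The cost is some extra analysis work and published per-act inputs. No new trial data are needed. If infection-specific inputs were always intended, step 2 is a change of wording only.

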### Intervention

All participants receive four HIVRR sessions and those assigned to the combination HIVRR+MF treatment arm receive an additional 30 sessions, including (1) six training sessions focused on financial literacy, (2) 24 sessions of vocational training in hairdressing, sewing, or manicurist professions, as well as (3) a matched savings program which incentivizes them to accumulate assets for small business development or job/vocational training. The NOVA intervention period lasts a total of 3 months post randomization, with intervention activities lasting for 2 weeks in the control arm, and for the full 3 months in the treatment arm. A brief description of each intervention component is provided below:

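### The claim that bias common to both arms cancels in the ICER is true only for additive errors, and the one robustness check named carries none of the trial's sampling uncertainty in the effect

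*Protocol article*

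**What the plan says.** All of this stands in the Cost-effectiveness analyses section of the protocol article, unless another place is named.

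- **Outcomes.** "Cost-effectiveness of the intervention will be analyzed based on STI infections and number of HIV and HCV cases averted over the 12-month period".
- **Ratio.** The ICER is the cost difference between arms divided by the effectiveness difference, (Ci − Cj)/(Eik − Ejk), for each outcome k.
- **Claim about bias.** "This approach safeguards validity against any biased measurements of cost or effectiveness that are common to both" arms; the reason given is that such errors cancel.
- **Effectiveness.** HIV, STI and HCV transmissions averted come from a Bernoulli process model, described as "the difference in risk-behavior frequencies times HIV transmission probabilities per act".
- **Robustness.** "One-way sensitivity analyses will use a range (e.g., 95% CIs) of HIV and HCV rates in the target population", and the stated purpose is a range "that may be compared to results to assess the robustness of estimates".
- **Use.** "Policymakers can easily and directly compare" the ICER with the metrics they already have, "to assess the added benefit of the microfinance intervention".

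The Intervention section adds that "those assigned to the combination HIVRR+MF treatment arm receive an additional 30 sessions", on top of the four sessions that both arms get. The incremental cost is therefore taken as positive below.

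**The concern.** Two statements in this section need correcting or strengthening.

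First, the sentence on cancellation covers any bias shared by the arms. A difference removes a shared constant. It does not remove a shared multiplier, and the effectiveness model in the same section is a product. Its main inputs are self-reported act counts and per-act probabilities, and errors in these are naturally proportional. The Challenges and limitations section itself recognizes reporting bias for stigmatized behaviors.

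Second, the section names its robustness check, its inputs and its purpose. The inputs are HIV and HCV rates in the population. The quantity that decides whether any infection was averted is the between-arm difference, which is estimated from the trial with sampling error, and the named check does not vary it. STI is a cost-effectiveness outcome and the one that fixes the sample size, yet no STI input is in the named range.

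At stake is a cost per infection averted that is offered to policymakers for direct comparison, with a stated protection that it does not have and a range that omits a main source of uncertainty.

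**Working it through.** **1. Which common errors cancel.** Let the true effects be Ei and Ej.

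- Additive error a in both arms: (Ei + a) − (Ej + a) = Ei − Ej. It cancels.
- Proportional error r in both arms: rEi − rEj = r(Ei − Ej). The ICER becomes (Ci − Cj)/[r(Ei − Ej)], that is, 1/r times its true value.
- A common proportional error s in costs multiplies the ICER by s. With both errors the factor is s/r, which is 1 only if s = r.

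The article gives no reporting fraction, so r is shown over a range: r = 0.9 gives 1/0.9 = 1.11 (+11%); r = 0.7 gives 1/0.7 = 1.43 (+43%); r = 0.5 gives 1/0.5 = 2.00 (+100%). This is exact for the product form and approximate for a Bernoulli model with small per-act risk.

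One factor can be taken from the article. Table 2 gives a *Mycoplasma genitalium* sensitivity of 76.5% (50.1–93.0%) and a specificity of 100%. If assayed infections are counted, with equal sensitivity in both arms and specificity taken as 100%, the detected difference for that infection is 0.765 of the true one. The cost per case is then overstated 1/0.765 = 1.31-fold (1/0.930 = 1.08 to 1/0.501 = 2.00).

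**2. What the named check moves.** In the product form, with population rate q, per-act probability β and mean risk acts n:

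Ei − Ej = qβ(nj − ni), and SE(Ei − Ej) = qβ × SE(nj − ni).

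The factor qβ drops out of the ratio of effect to standard error. At every q in the range the estimate is equally many standard errors from zero. The check shows how the ICER scales with q and says nothing about how well the trial estimated nj − ni.

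**3. Size of the omitted uncertainty, on the plan's own figures.** Inputs from Power and sample size: STI incidence 0.144 (HIVRR) and 0.043 (HIVRR+MF), two-sided α 0.05, power 80%, ICC 0.01, 20% attrition, 175 randomized per arm. Cohorts hold six to eight women.

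Reproducing the plan first: the pooled two-proportion formula without continuity correction gives 130 per arm.

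- Cohorts of 8: 130 × 1.07 = 139.1, so 140; 140/0.8 = 175 per arm, 350 in total.
- Cohorts of 7: 130 × 1.06 = 137.8, so 138; 138/0.8 = 172.5, so 173 per arm, 346 in total.
- Cohorts of 6: 344 in total by the same steps.

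The stated 350 is reproduced. (The section also states a relative risk of 0.25, whereas 0.043/0.144 = 0.30. The two incidences are used here because they give the sample size.)

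Now the interval, with 175 × 0.8 = 140 per arm and variance inflation 1 + (7 − 1) × 0.01 = 1.06:

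- Difference: 0.144 − 0.043 = 0.101.
- SE = √[1.06 × (0.144 × 0.856 + 0.043 × 0.957)/140] = √[1.06 × 0.164415/140] = 0.0353.
- 95% CI: 0.101 ± 1.96 × 0.0353 = 0.032 to 0.170.
- ICER relative to its point value, incremental cost fixed: 0.101/0.170 = 0.59 to 0.101/0.032 = 3.2.

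This is the case in which the trial observes the full effect that it was designed for. With a smaller observed effect the lower limit nears or crosses zero and the ratio has no finite upper limit.

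**The case against.** **The article is condensed.** It does not say that the one-way analysis is the sole uncertainty analysis, and bootstrap or acceptability-curve detail is often left to a fuller economic plan. This stands. A reader might infer that no other analysis is planned; the text supports only that this is the one check named. No other plan, however, can make the cancellation sentence true.

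**Rates may mean something else.** Elsewhere the article uses the word for new cases in the trial. If arm-specific rates were varied over their intervals, effect uncertainty would enter. The reference to the target population favors background rates, but the wording could be clearer.

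**The sign of the incremental effect.** A reader might infer that varying the rates can never change it. That is exact for the product form. In a per-partner Bernoulli model it can fail: at a per-act probability of 0.01, one partner with 60 acts against three partners with 18 acts each changes order between rates of 50% and 75%. The reversal comes from exposure pattern and not from sampling error, so it does not make the check a test of effect uncertainty.

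**A null trial passing as robust.** A reader might add that about half of no-effect trials would show a favorable ICER. That is true of any unbiased point estimate by symmetry and does not measure harm from this check. Nor would a null result be hidden: the Data analysis section commits to 95% CIs and p values for the infection and behavior outcomes, with clustering handled by GEE. What remains is that these intervals are not said to be carried into the ICER.

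**A narrow range.** The article leaves the range open, so it cannot be called narrow. If the susceptible share is included, the effect scales with q(1 − q); HIV rates of 10% and 50% give 0.09 and 0.25, a 2.8-fold span. The STI figures above are also a different outcome from the HIV and HCV ones, so they show scale only.

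**Conclusion.** The point holds in two parts. The statement that common bias cancels is wrong as written: it is true for additive errors equal in both arms and false for proportional ones, which multiply the ICER by 1/r. The values of r used for reporting are illustrations, because the article gives none.

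The named robustness check, in the section's own product form, is silent on the sampling uncertainty of the incremental effect and omits STI. At the plan's STI assumptions, that uncertainty alone spans about 0.6 to 3.2 times the point ICER. This rests on 140 women per arm, variance inflation of 1.06, a normal approximation and a fixed positive incremental cost.

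The documents do not show that other uncertainty analyses are excluded, or that a null trial would be reported as a robust gain. Cost-effectiveness is a secondary aim, so primary inference and sample size are untouched. The change should still be made, because the ratio is meant for policy comparison.

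**What to change.** - Limit the cancellation sentence to additive errors of equal size in both arms, and say that proportional errors rescale the ICER.
- Base the main uncertainty statement on the trial data. Resample whole cohorts within arm and recompute the incremental effect in each resample, together with incremental cost where cost varies by cohort or participant.
- Report incremental net benefit with a 95% interval over a range of willingness to pay, or an acceptability curve, for STI, HIV and HCV. Both stay defined when the effect is near zero; the ICER does not.
- Keep the one-way analyses as a supplement. State that the rates are background rates, if that is meant, and add per-act probability and reporting fraction to the inputs varied.

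The cost is some extra programming on data already being collected and a few reworded sentences. The drawback is a wider and less favorable stated range.
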